### Theoretical framework and approach

The Consolidated Framework for Implementation Research (CFIR) was used to guide study aims and assess the implementation context (elementary school settings) and evaluate implementation progress (monitor educators’ *RR *use) [43]. Specific CFIR components included: 1) the intervention (*RR*); 2) inner setting (schools); 3) the individuals involved (educators and school-based teams); 4) the implementation process; and 5) outer setting (e.g., school district variables associated with cost). The implementation strategies comprise coaching, once weekly coaching in *RR* and school-based teams, monthly facilitation of school-based teams that identifies, monitors, selects, and matches implementation strategies to address common barriers to *RR *implementation. We theorize that: 1) coaching targets the educator-level mechanism [44], skill acquisition (learning to use *RR*); and 2) school-based teams target school-level mechanisms, implementation leadership and climate, which will directly impact educators’ use of *RR* with fidelity that ultimately will lead to improved student outcomes (Fig. 1). Implementation leadership and climate are proposed school-level mediators in the theory of change. We will measure three implementation outcomes: 1) *fidelity*, the degree to which *RR* is used in the way it was designed during the active implementation phase (primary outcome); 2) *sustainment*, the extent to which *RR* use is maintained the following school year; and 3) *cost,* the extent of resources needed for an implementation effort [45] and three student outcomes: 1) *peer engagement*; 2) *social network inclusion;* and 3) *social skills*. We focus on social outcomes that are most relevant to school inclusion [4, 6, 6, 8].

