#### Study purpose and aims

The purpose of this study is to test whether an educator-level implementation strategy, *coaching*, with or without a school-level implementation strategy, *school-based teams*, will maximize educators’ use (fidelity) of *RR* and student outcomes.

**Primary Aim 1:** Test the effect of coaching with school-based teams (vs. coaching only) on educators’ implementation and student social outcomes. We hypothesize that (a) coaching with school-based teams will result in greater *RR* fidelity (primary outcome) at the end of Semester 2 and sustainment the following school year, and (b) both arms will result in improved peer engagement and social skills from baseline to end of Semester 2, but coaching with school-based teams will improve student social network inclusion at the end of Semester 2 more than coaching.

**Secondary Aim 2: (Mediation)** Test the extent to which implementation leadership and climate will mediate the effect of coaching with school-based teams vs. coaching only on implementation and student outcomes. We anticipate that both implementation leadership and climate will mediate the relationship between coaching with school-based teams and coaching only and *RR* fidelity and student social outcomes at the end of Semester 2.

**Secondary Aim 3: (Moderation)** Explore if subgroups of students will benefit more from *RR *implementation by examining whether child-level characteristics (e.g., age, gender, autism classification) moderate the effect of coaching with school-based teams vs. coaching only on implementation and student outcomes. Based on our previous research [46], we anticipate that younger vs. older, female vs. male, or allistic vs. autistic students in schools that receive coaching with school-based teams will have better student social outcomes compared to coaching only.

**Secondary Aim 4**: Estimate the incremental costs of coaching with school-based teams versus coaching only to determine the most cost-effective approach.

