#### Data collection

Data will be collected during the following timepoints: T1 = baseline; T2 = Exit of *RR* 1; T = 3 End of Year 1; T4 = fall, the following school year; and T5 = spring, the following school year***.*** At baseline, we will collect demographics from all participants, as well as time in inclusion from teachers and autism symptomatology from caregivers. We also will ask caregivers to rate the quality of play for their child at all timepoints (T1-T5). A masked rater will code *RR* fidelity and peer engagement at all timepoints (T1-T5) provided the student remains at the school the following year. Educators and school-based teams members will be asked to complete acceptability and a cost survey at T1-T5 and rate sustainment at T4-T5. All consented students will be administered the Friendship Survey (~ 5–10 min) at T1-T3, and teachers will be asked to complete a measure of social skills per enrolled student at T1-T3. We will continue to collect implementation outcomes the following school year. Educators, teachers, and school-based team members will be asked to rate implementation leadership and climate and team processes at T1-T5. Participants will be assigned a numerical code. De-identified data will be entered into REDCap, and all efforts will be made to prevent risks. Progress reports will be submitted as required. De-identified data will be shared with the National Database for Autism Research twice a year.

Schools will receive an initial 60–90-min didactic at the start of the school year, followed by 20–30 min of weekly coaching. *RR* experts will provide both the initial training and weekly coaching via Zoom. Research staff will receive training to reliably administer measures and achieve coaching and school-based teams fidelity.

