### Data analysis

All subjects, once randomized, will be included in the intent-to-treat sample, and every effort will be made to collect all primary and secondary outcomes even if the participant (educator, school personnel, or student) does not engage in randomly assigned treatments.

#### Primary aim 1

Primary Aim 1 analysis will contrast coaching with school-based teams vs. coaching only on change in *RR* fidelity (primary outcome) and students’ peer engagement (secondary outcome) from T1-T5. Generalized linear mixed models (GLMM) will be used to analyze change in T1-T5 for *RR* fidelity and sustainment as well as peer engagement and from T1-T3 for all other social outcomes. Separate models will be fitted for each primary and secondary outcome and a piecewise-linear model with potential knot(s) at T2 and T3, will be used to model the temporal trajectories across the study as the trajectories of the outcomes may occur at the end of each semester. The analysis will fit a GLMM with fixed effects for the intercept, time, and a group-by-time interaction. The GLMM will include random effects for the intercept and time (slope) and model the correlation between the two random effects. All outcomes will be assessed for normality. If outcomes are non-normally distributed, other distributions will be assumed or transformations of the outcomes will be considered. The GLMM also can be extended to model the nesting effects (e.g., educators nested within schools or students nested within classrooms or educators). The GLMM will adjust for the following baseline measures X when evaluating the primary outcome—*RR* fidelity: site and years of experience at current position. For models evaluating student outcomes, the GLMM will adjust for X: site and child’s age. The primary aim contrast in this study is the between groups difference in change in outcomes from T1-T5 for *RR* fidelity and sustainment as well as playground engagement and between group differences in changes from T1-T3 for all other student outcomes.

#### Secondary aim 2

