#### Sample size and power considerations

The sample size for the study (*n* = 121 educators, *n* = 118 students in *n* = 55 elementary schools) was determined based on statistical power for the Primary Aim 1 contrast, a between implementation strategies (coaching with school-based teams vs. coaching only) mean comparison in change in *RR* fidelity (primary outcome) from T1-T3. Based on a Type-I error rate of 5%, a within-person correlation in paraeducator fidelity of ICC = 0.36 (based on preliminary data), a total number of 98 educators are needed to detect a difference of at least 0.15 in the comparison of slopes in educator’s *RR* fidelity with 80% power. After accounting for an estimated attrition rate of 10% and a 10% variance inflation factor for clustering by school, a total number of *N* = 121 is needed. Similarly, for our Primary Aim 1 secondary outcome, peer engagement, assuming a Type-I error rate of 5%, a within-person correlation in students’ joint engagement of ICC = 0.18 (based on preliminary data), a total number of 118 students are needed to detect a difference of at least 14% in total time spent in joint engagement in the comparison of slopes in joint engagement between coaching with school-based teams vs. coaching only with 80% power and 10% attrition and 10% variance inflation factor for clustering by school.

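### The primary contrast for RR fidelity has two windows: powered on change T1-T3, analysed as change T1-T5, so the stated 80% power does not describe the named test

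*Protocol article*

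**What the plan says.** Four places in the protocol article bear on the window for the primary outcome.

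- **Data analysis, Primary aim 1.** The opening sentence sets the comparison of arms on fidelity change over T1-T5. The closing sentence repeats it: "The primary aim contrast in this study is the between groups difference in change in outcomes from T1-T5 for" RR fidelity, sustainment and playground engagement. T1-T3 is kept for the remaining student outcomes. The time course is to be handled by "a piecewise-linear model with potential knot(s) at T2 and T3".
- **Sample size and power considerations.** The trial is sized on the Primary Aim 1 contrast, described as the between-strategy comparison of change in "fidelity (primary outcome) from T1-T3". The result is that "a total number of 98 educators are needed to detect a difference of at least 0.15 in the comparison of slopes", with 80% power. This becomes 121 after allowances for attrition and clustering.
- **Study purpose and aims, Primary Aim 1.** The hypothesis is greater "fidelity (primary outcome) at the end of Semester 2 and sustainment the following school year".
- **Theoretical framework and approach.** Fidelity is the degree to which RR "is used in the way it was designed during the active implementation phase (primary outcome"), and sustainment is a separate outcome for the following school year.

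The Data collection section fixes the calendar: "T = 3 End of Year 1; T4 = fall, the following school year; and T5 = spring, the following school year".

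**The concern.** The same named contrast, for the same primary outcome, has two definitions. T1-T3 asks whether adding school-based teams raises fidelity within the first school year. T1-T5 asks whether the arms differ in change by the spring of the next school year. These are different estimands. If the arm difference alters in year 2 they need not agree, and a real T3 benefit that had gone by T5 would show under one and not under the other.

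The power statement belongs to the first quantity only. A reader who takes the Data analysis section as the definition of the primary test has no power figure for it. The T1-T5 window also puts the active phase and the sustainment year into one number, although the framework section separates them.

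**Working it through.** **Side by side.**

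| Section | Window for fidelity |
|---|---|
| Theoretical framework | active implementation phase; next year is sustainment |
| Aims, Primary Aim 1 | end of Semester 2 (T3, by inference from End of Year 1) |
| Sample size | T1-T3, explicit |
| Data analysis, Primary aim 1 | T1-T5, stated twice |

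The last row conflicts with the other three. A further sign that the contrast sentence needs revision is that it also promises T1-T5 change for sustainment, which Table 2 collects only at T4-T5.

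**The plan's own figure.** Inputs from the sample size section: 98 evaluable educators, 10% attrition, 10% clustering inflation, within-person correlation 0.36, slope difference 0.15, type I error 5%, power 80%.

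- Inflation: 98 / (0.9 × 0.9) = 120.99, so 121. This reproduces.
- Core: for a two-arm slope comparison under compound symmetry, n per arm = 2(z₀.₉₇₅ + z₀.₈₀)² SD²(1 − ρ) / (Sxx d²). With (1.96 + 0.84)² = 7.85, ρ = 0.36 and three equally spaced visits (Sxx = 2), 49 per arm requires SD = 0.468 if 0.15 is per timepoint, or 0.234 if it is the total over T1-T3. The article gives no SD, so the 98 cannot be checked independently. The results below do not depend on it, because they are calibrated to the stated 80%.

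**Power of a T1-T5 contrast.** Assumptions that are not in the document: two-sided 5%, 49 per arm, compound symmetry, equally spaced visits, and the year-2 course in each row. Calibration: the T1-T3 test has expected z = 2.80. Let d be the arm difference gained per visit up to T3, so the T3 difference is 2d.

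- Raw T5-T1 change: its variance equals that of T3-T1, so z = 2.80 × (T5 difference / 2d).
- Straight slope over five visits: Sxx = 10 instead of 2, so z = 2.80 × (fitted slope / d) × √(10/2). Visit weights are (−2, −1, 0, 1, 2)/10.
- Power = Φ(z − 1.96) + Φ(−z − 1.96).

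| Arm difference at T1 to T5 | Fitted slope | z, slope | Power, slope | z, raw | Power, raw |
|---|---|---|---|---|---|
| 0, d, 2d, 3d, 4d (keeps diverging) | 1.00d | 6.26 | >99% | 5.60 | >99% |
| 0, d, 2d, 2d, 2d (held) | 0.50d | 3.13 | 88% | 2.80 | 80% |
| 0, d, 2d, 1.5d, d (half lost) | 0.25d | 1.57 | 35% | 1.40 | 29% |
| 0, d, 2d, d, 0 (gone) | 0 | 0 | 5% | 0 | 5% |

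Extra year-2 loss lowers these. With 40 per arm, the held row becomes 81% / 72% and the half-lost row 29% / 24%.

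**The case against.** The strongest defence is that the model can already deliver the right contrast. A piecewise-linear model with a knot at T3 separates the first year from the second, and the single time and group-by-time terms listed afterwards can be read as shorthand for the piecewise terms. Final knot choice is the kind of detail an SAP settles. That is fair as far as it goes, and the wording does not show that one straight T1-T5 slope will be fitted. It does not remove the conflict: the knots are only potential, and the contrast the text names is T1-T5.

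Several stronger readings are tempting but unsupported.

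- *The trial is underpowered.* Nothing in the article says the arm difference fades, and the hypothesis expects better sustainment with teams. If the T5 difference were 1.25 times the T3 difference, raw-change power would be about 94% (z = 3.50). Power for T1-T5 is unstated and could lie on either side of 80%.
- *A five-visit slope halves the effect and so loses power.* When the T3 difference is held, the fitted slope is half the active-phase slope, but five visits estimate it more precisely and power rises to about 88% under compound symmetry. The planned random slopes would shrink that gain.
- *T1-T5 does not test the hypothesis.* Hypothesis (a) also covers the following year. The fair criticism is that T1-T5 does not isolate the Semester 2 part.
- *Table 4 proves that support stops at T2.* Its marks could denote visits or periods starting at those visits, and the article does not settle which. The point here does not rely on it.
- *The window is open to choice after the data are seen.* That depends on the SAP and registry entry, which are not shown.

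**Conclusion.** The contradiction is real and concerns the primary estimand. The sample size section and the Data analysis section give the Primary Aim 1 fidelity contrast different windows, and no text reconciles them. The hypothesis and outcome definition side with T1-T3, subject to the inference that the end of Semester 2 is T3; the T1-T3 window in the sample size section is explicit.

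The stated 80% does not carry over to T1-T5. The size of the mismatch depends on a year-2 course that the article does not state: the scenarios span 5% to over 99%. That range shows that the figure is unknown; it is not a forecast of a shortfall.

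**What to change.** In Data analysis, Primary aim 1, state the primary estimand as the between-arm difference in change in RR fidelity from T1 to T3. Estimate it as a contrast from the model using all visits, with the T3 knot fixed in advance, or with an equivalent form such as categorical visit. Make the T4/T5 fidelity contrast a named secondary sustainment analysis. The sample size text can then stay at T1-T3, and its 80% applies to the named contrast as the plan intends.

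If the sponsor does intend T1-T5 as primary, the hypothesis and the definition of the primary outcome must be changed to match. The power statement must also be recalculated for that contrast, with the assumed year-2 course and year-2 attrition stated.

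The first route costs only wording, since fidelity is already scheduled at all five timepoints. The article reports no enrolment as of September 2024. Any SAP or registry entry should be checked for the same window.

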#### Sustainment

The extent to which *RR* is sustained will be calculated using the Provider Report of Sustainment Scale (PRESS) [53] at T4 and T5. Internal consistency is high (α = 0.95).

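### Sustainment is to be analysed as change from T1 to T5, but the scale that measures it is collected only at T4 and T5

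*Protocol article*

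**What the plan says.** Under Data analysis, Primary aim 1, sustainment is placed twice among the outcomes followed from T1 to T5. The first sentence sets the model: "Generalized linear mixed models (GLMM) will be used to analyze change in T1-T5 for *RR* fidelity and sustainment as well as peer engagement". The last sets the contrast as the between-group difference "in change in outcomes from T1-T5 for *RR* fidelity and sustainment as well as playground engagement". One model form is given for all outcomes: "Separate models will be fitted for each primary and secondary outcome", using "a piecewise-linear model with potential knot(s) at T2 and T3". The fixed part is stated as "The analysis will fit a GLMM with fixed effects for the intercept, time, and a group-by-time interaction", and the random part as "The GLMM will include random effects for the intercept and time (slope) and model the correlation between the two random effects". No other model or contrast is given for sustainment.

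The schedule differs. The Sustainment paragraph under Measures says the outcome is calculated from the "Provider Report of Sustainment Scale (PRESS) [53] at T4 and T5". The Data collection section has educators and school-based team members "rate sustainment at T4-T5". Table 2 and Table 4 agree. The theoretical framework section defines sustainment as a matter of the following school year, and Aim 1 hypothesis (a) expects the team arm to do better on it in that year.

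**The concern.** A change from T1 needs a T1 value, and sustainment has none. By its own definition it could not have one, because there is nothing to sustain before training. The T1-T5 wording is therefore wrong for this outcome, and the model form built for five visits is carried over to an outcome with two.

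Sustainment is half of hypothesis (a), and it is one of the effectiveness measures listed for the incremental cost-effectiveness ratios. Both uses need a defined between-arm effect. As the text stands, the analyst would have to decide after the PRESS data exist which contrast to report, and the candidates can give very different answers from the same data.

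**Working it through.** **Inputs.** From the article: PRESS at T4 and T5 only; fixed effects of intercept, time and group-by-time; potential knots at T2 and T3; a correlated random intercept and slope. My assumptions: visits coded T1 = 0 to T5 = 4, equal PRESS variance at T4 and T5, equal arms, and a T4-T5 correlation r. The article gives no r for PRESS. I use 0.36, borrowed from the within-person fidelity correlation in the sample size section, and show a range.

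**1. Covariance parameters, one rater, times 3 and 4.** With intercept variance a, covariance b, slope variance c and residual variance s:

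- Var(T4) = a + 6b + 9c + s
- Cov(T4, T5) = a + 7b + 12c
- Var(T5) = a + 8b + 16c + s

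There are three equations and four unknowns (rank 3 of 4), so the parameters are not identified. With all five visits there would be 15 moments and rank 4 of 4.

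**2. Fixed effects, T4 and T5 rows only.** Two arms by two visits give four cell means.

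- One knot at T2 or T3: 5 columns, rank 4.
- Both knots: 7 columns, rank 4.
- Arm main effect added: rank 4 of 6 (one knot) or 4 of 8 (both), and the T1-T5 difference in change is not estimable.
- No knot, arm main effect present: a T1-T5 number exists, but it is the T4-T5 slope extrapolated back over three unmeasured visits.
- No arm main effect, as written: a T1-T5 number exists because the model forces the arm means to be equal at time 0, that is, at T1, where nothing was measured.

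**3. What is reported for a true one-point team-arm advantage at both visits.**

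- T4-T5 change with an arm main effect: 1 − 1 = 0.
- As written, no knots, time 0 to 4: the arm difference is forced to be g × time. Generalised least squares on differences (1, 1) at times (3, 4) gives g = 7(1 − r)/(25 − 24r). At r = 0.36, g = 4.48/16.36 = 0.274 per visit, and the T1-T5 contrast is 4 × 0.274 = 1.10. At r = 0 it is 4 × 7/25 = 1.12. At r = 0.6 it is 4 × 2.8/10.6 = 1.06.
- As written, but time recoded T4 = 0 and T5 = 1: g = 1 − r = 0.64 at r = 0.36.

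The same data yield 0, 0.64 or 1.10, according to time origin and whether an arm main effect is included.

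**4. Who rates PRESS.** Table 2 and Data collection name educators and school-based team members. The article plans 83–138 other personnel for the teams, about 3–5 per team. Half of 55 schools is 27.5; 27.5 × 3 = 82.5 and 27.5 × 5 = 137.5. The count matches teams in one arm only, so team-member ratings appear to have no counterpart in the coaching-only arm.

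**The case against.** The best defence is that this is one generic model paragraph in a condensed article. The knots are only potential, nesting is offered as an extension, other distributions are allowed, and dropping a random slope for a two-visit outcome is routine detail for an analysis plan. Much of that stands for the random effects. The identification failure is specific to a rater-level Gaussian slope with a free residual variance. A slope placed only at school level, with at least two raters per school, would be identified (rank 4 of 4, or 5 of 5 with a rater intercept), and eligibility requires at least two educators per school. A reader might infer that the model cannot be estimated in any form; that goes too far. But the article makes nesting optional, and none of these allowances creates a T1 value. The text separates T1-T5 outcomes from T1-T3 outcomes and puts sustainment in a window it does not have, so the error is in what is stated.

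A reader might also infer that, because the stated model has no arm main effect, a constant team-arm advantage would be missed and reported as null. The opposite is true: without that term the level difference is pushed into the group-by-time coefficient. Exactly zero arises only when an arm main effect is added and the T4-T5 change is taken as the contrast.

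Finally, sustainment is not the primary outcome, its collection times are unambiguous, and observed fidelity continues through T4 and T5. This limits the weight of the point. It does not repair the sustainment analysis, because the article assigns sustainment to PRESS.

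**Conclusion.** The point holds as an internal contradiction: the stated sustainment contrast is a T1-T5 change, and no such change is measured. The two placements of sustainment in the T1-T5 group conflict with all four statements of the PRESS schedule.

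The consequence is an undefined result. For a constant one-point advantage, the reported figure ranges from 0 to about 1.1 depending on unstated choices. The upper figure assumes r = 0.36 and equal variances, and moves only from 1.12 to 1.06 as r goes from 0 to 0.6. It also rests on equal arm means at an unmeasured T1. Neither a T4-T5 change nor an extrapolated T1-T5 change directly tests hypothesis (a), which concerns a difference in level during the following year.

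The defect is confined to sustainment and the cost-effectiveness ratios that use it. Fidelity and peer engagement are collected at T1-T5, and the sample size does not rest on sustainment.

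**What to change.** Remove sustainment from the two T1-T5 sentences and give it its own analysis:

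- **Contrast:** the between-arm difference in mean PRESS level at one prespecified contrast, for example the T4-T5 average. In the one-point example this returns 1 whatever the time coding.
- **Model:** arm, visit (T4, T5), arm-by-visit and the planned site adjustment, with random intercepts for school and rater and no random slope. At rater level this is 2 variance parameters against 3 moments. The school variance is identified from the covariance between educators in the same school.
- **Raters:** base the between-arm comparison on educators, who exist in both arms, and report team-member ratings descriptively. Pooling both would confound arm with rater type.
- **Economic evaluation:** use the same contrast for the sustainment ratio.

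The cost is protocol and analysis-plan wording, with no new data. The downside is that team-member PRESS ratings do not contribute to the comparison. The article reports no enrolment as of September 2024. The change should be made and dated before any T4 ratings are analysed.

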#### Inclusion/exclusion

We will recruit *n* = 121 educators who attend recess and are school district employees, to ensure they have the capacity to participate in research activities. We also will recruit *n* = 55 general and/or special education teachers to complete study measures about students and school-level constructs and *n* = 83–138 other school personnel (e.g., administrators, teachers) to serve on the school-based teams (approximately 3–5 participants). Participants will remain in the study for 18 months unless they withdraw or change jobs. School personnel involved with *RR* coaching will receive $50 for their data completion. School personnel involved with school-based teams will receive $25 per session and $25 for their data completion. Teachers will receive $25 for their data completion and an additional $10 per student per data collection timepoint.

We will recruit 118 autistic students and allistic classmates. Autistic students will be included if they: 1) have a documented autism classification; 2) are between the ages of 5–12 and enrolled in Kindergarten through 5th grade; and 3) share a recess period with allistic peers. Allistic classmates will be included if they are: 1) isolated or peripheral on their classroom social network; and 2) require support during recess. Autistic students and their peers without an available educator supporting recess will be excluded. Participants will not be excluded given their sex, gender identity, age, or racial/ethnic background, and will not be asked to disrupt any other service utilization.

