### Procedures

Recruitment in schools will include an informational email and video about the study, *RR*, coaching, and school-based teams. We will meet with school administrators via Zoom to share study information, participation requirements, and answer questions. We will then meet with educators to obtain consent and subsequently ask teachers to send recruitment materials (electronic/paper) to caregivers of focal students and classmates to participate in the Friendship Survey. The results of the Friendship Survey will determine social network inclusion status (isolated, peripheral, secondary, and nuclear). We will invite classmates who are classified as isolated, rejected, or peripheral and who may need additional support at recess (*n* = 1–2 per school) into the study.

An independent statistician will randomize all schools. The randomization (coaching with school-based teams vs. coaching only) has equal assignment probability to each group. Randomization will be stratified on the number of educators who will deliver *RR* (educators = 2 vs. > 2). Unmasking of randomization will not be permissible.

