Secondary Aim 2 aims to evaluate whether implementation leadership and climate mediates the effect of coaching with school-based teams (vs. coaching only) on *RR *fidelity and student outcomes. We will extend the regression models from Primary Aim 1 to evaluate the mediation effect [78]. The analysis will result in estimates of and confidence intervals for the direct effects for coaching with school-based teams (vs. coaching only) on outcomes and the indirect effects of the strategies on outcomes via implementation leadership and climate.

#### Secondary aim 3

Secondary Aim 3 aims to explore whether child characteristics collected at T1 moderate the effect of coaching with school-based teams vs. coaching on primary outcomes. GLMM will be expanded to include a third order interaction term (and all lower order interactions) of child characteristics (age, gender, autism classification) with strategy group (coaching with school-based teams vs. coaching only) with time (T1-T3) to evaluate the moderation effect.

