#### Supplemental analysis

We will explore whether the effect of implementation strategies on student outcomes differ by 1) autistic students versus classmates who are peripheral/isolated on their social network; and 2) demographic characteristics (e.g., age, gender, and race/ethnicity) by extending the moderation analysis in Secondary Aim 3.

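### The Aim 3 autism moderator sets autistic students of any network status against allistic classmates enrolled for low status; label the contrast that way and check it against T1 inclusion

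*Protocol article*

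**What the plan says.** The Inclusion/exclusion section sets different entry rules for the two student groups. For autistic students it begins "Autistic students will be included if they: 1) have a documented autism classification; 2) are between the ages of 5–12" and then adds grade and a recess shared with allistic peers. The Autism symptomatology section adds a Social Communication Questionnaire threshold. None of these concerns network status. For the other group: "Allistic classmates will be included if they are: 1) isolated or peripheral on their classroom social network; and 2) require support during recess". The Procedures section says that the Friendship Survey determines network status, and it widens the category: "We will invite classmates who are classified as isolated, rejected, or peripheral and who may need additional support at recess".

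Aim 3, under Study purpose and aims, carries a directional expectation: "allistic vs. autistic students in schools that receive coaching with school-based teams will have better student social outcomes" than under coaching only. In the Data analysis section, Secondary aim 3 gives the model: "GLMM will be expanded to include a third order interaction term (and all lower order interactions) of child characteristics (age, gender, autism classification", crossed with strategy group and time. Primary aim 1 lists the adjustment variables for student outcomes as site and the child's age. The Supplemental analysis extends the same moderation model and names the first contrast as "autistic students versus classmates who are peripheral/isolated on their social network". T1 network status is neither a covariate nor a moderator in any of these places.

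**The concern.** One level of the moderator is selected on baseline social standing and the other is not. The selecting instrument also supplies the baseline of a student outcome, because the Friendship Survey yields social network inclusion at T1 to T3. That score is a student's centrality divided by the classroom maximum. It cannot exceed 1, so students who start low have more room to rise. If the team effect differs by starting level and the two groups start at different levels, the autism × arm × time term is non-zero even when autism itself changes nothing.

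At stake is how a moderation result is read. Autism classification is a named moderator with a predicted direction, and the abstract says that findings may guide scale-up in districts. A difference in benefit that came from baseline isolation could be reported as a difference by autism.

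**Working it through.** The document gives no figure for this moderation, so there is none to reproduce. The check asks how large a false autism term the stated model could return.

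**Inputs from the protocol article.** There are 118 students, and the split between autistic and allistic is not given. The inclusion score runs from 0 to 1. Isolated means no nominations, and peripheral means the bottom 30% of the classroom.

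**Inputs assumed, not in the documents.** d is the team effect on change in the inclusion ratio for students who are isolated or peripheral at T1, with no effect in others, whatever their autism status. p is the share of autistic students who are isolated or peripheral. All allistic classmates are taken to be so.

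**Step 1, simple formula.** The mean team effect is d in allistic classmates and d × p in autistic students. The apparent moderation (allistic minus autistic) is d − d × p = d × (1 − p), against a true value of 0. With d = 0.10:

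- p = 0.3: 0.10 × 0.7 = 0.07
- p = 0.5: 0.10 × 0.5 = 0.05
- p = 0.8: 0.10 × 0.2 = 0.02
- p = 1.0: 0

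**Step 2, chance of a false positive at that size.** Assume half of the students are autistic, equal arms, a residual SD of 0.25 for change, and no clustering or attrition. The standard error of the interaction is 4 × 0.25 / √118 = 0.092. The three non-zero values above would be significant at 5% in about 12%, 8% and 5.5% of trials.

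**Step 3, steeper scenario by simulation.** There were 1,500 replicates per setting with n = 118, the same SD and the same split. The team effect fell by 0.5 per unit of T1 inclusion and did not depend on autism. Low-status students were uniform on 0–0.3 (mean 0.15) and the others uniform on 0.3–1 (mean 0.65). The gap in effect is 0.5 × (0.65 − 0.15) = 0.25, which is 2.5 times the d of Step 1. The formula gives −0.25 × (1 − p), autistic minus allistic.

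| p | Formula | Planned terms: mean estimate | Rejected at 5% |
|---|---|---|---|
| 0.3 | −0.175 | −0.176 | 42% |
| 0.5 | −0.125 | −0.126 | 25% |
| 0.7 | −0.075 | −0.070 | 11% |
| 0.9 | −0.025 | −0.026 | 6% |
| 1.0 | 0 | −0.001 | 5% |

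Two repairs were tried: adding T1 inclusion with its arm interaction, and restricting autistic students to those of low T1 status. Either one brought the mean estimate to between −0.001 and 0.005, with rejection of 4% to 6%. When the team effect was constant across T1 inclusion (slope 0), the planned terms gave 0.001 to 0.004 and rejection near 5% at every p. The enrolment difference does no harm unless the team effect varies with T1 status.

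**Limits.** The simulation treats a classroom percentile as if it were an inclusion ratio, which is a simplification. Its values should not be set against the 14% in the sample size section, because that figure is time in joint engagement, a different scale.

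**The case against.** Arm is randomised, so the autism × arm × time term validly describes how the team effect differs between the autistic students and the classmates who were enrolled. The aim is stated as exploratory, and the Supplemental analysis already names the comparison group accurately. This stands, and it is why the planned model can stay. What remains is that the aims and the Secondary aim 3 text use autism classification without that description.

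The assumed sizes may be high. The Background says that nearly one-third of an inclusive classroom is isolated or peripheral. The Discussion says that autistic students are less included than their allistic peers. So p probably exceeds 0.3, and the distortion shrinks accordingly. This also stands. With d = 0.10, false positives are only modestly above 5%, and the 42% figure needs a much steeper effect gradient.

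The premise that every allistic classmate is isolated or peripheral is not secure either, since Procedures also admits rejected classmates. Any repair has to say how they are handled.

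Finally, the article is condensed, and its examples of moderators are introduced as examples. A fuller plan may name more. That would excuse a missing detail. It does not remove the point, because the article names the model terms and gives the hypothesis in terms of autism.

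**Conclusion.** As written, the Aim 3 autism term mixes autism with baseline network standing, and the text does not describe the contrast that way. The size ranges from nothing to 0.07 on the 0–1 ratio under d = 0.10, and to about 0.18 under the steeper scenario. Both rest on assumed effects and on a share p that the documents do not give. The concern is clearest for social network inclusion. The documents give no figure linking network status to peer engagement or social skills that would carry it over to them. The primary fidelity result is not affected.

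A reader might infer three stronger things, and none is supported:

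- **The enrolment rule alone could confirm the hypothesis.** It cannot. The team effect must also vary with T1 status, and no section says that it does.
- **The distortion must favour the predicted direction.** It would if low-status students gain more. If better-connected students gain more, it runs the other way.
- **The two factors cannot be separated.** That is true of the stated model only. T1 inclusion is collected, and a supporting analysis can largely separate them.

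**What to change.** Keep the planned model and make two changes.

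1. **Label.** In the aims and in Secondary aim 3, describe the contrast as the Supplemental analysis does: autistic students versus isolated or peripheral allistic classmates, not an effect of autism as such. Mention the recess-support criterion too, since it also applies to classmates only and conditioning on network status does not remove it.
2. **Supporting analysis.** Using the T1 Friendship Survey, do one of the following. Either add the continuous T1 inclusion ratio with its interactions with arm and time, or repeat the contrast with autistic students restricted to those who meet the classmates' T1 network criterion. State in advance how rejected classmates are handled, because rejected is not one of the four network levels. Attribute moderation to autism only if it persists in this analysis.

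No new data are needed. The cost is precision. Under the restriction, with half of the students autistic and equal arms, the standard error grows by √((1 + 1/p)/2). That is 1.47 times at p = 0.3, 1.22 at p = 0.5 and 1.06 at p = 0.8, so 0.092 becomes about 0.136, 0.113 and 0.098. The cost is largest where the distortion is largest. The continuous version keeps all students but relies on the assumed form of the relation at inclusion levels where few or no allistic classmates are enrolled.
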